#### Secondary implementation outcomes/measures

2.7.2

##### Dose received

2.7.2.1

‘Dose received (exposure)’ will also be assessed by the number of logged workouts completed amongst participants, assessed at three- and six-months. Data relating to additional characteristics of ‘dose received (exposure)’ will also be evaluated at three- and six-months, including assessment of (i) changes in the workout difficulty time-period by individuals, (ii) whether app users engage in different workout types, training categories or chose workouts targeting specific body parts, (iv) number of goals set and met, (v) and setting where the workouts were undertaken (i.e., home versus park-based). ‘Dose received (exposure)’ is also operationalized as the proportion of participants logging at least one workout in the app, which will be assessed at three- and six-months.

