### Recruitment, randomization and blinding

2.2

We have developed a promotional campaign to promote outdoor gym use across both local government municipalities; this will serve as the primary recruitment strategy for the study. The campaign will employ strategies, used in the *ecofit* effectiveness trial [31] and other, similar studies [39], including print and broadcast media, letter drops to all households within the same or adjacent suburbs of each outdoor gym, school/work newsletters, and social media, to promote the *ecofit* app and outdoor gym use. The promotional information will also emphasise the benefits of RT.

Randomization of the park location has already been conducted. Each outdoor gym was pair-matched based on the socioeconomic status of the area surrounding the facilities (high versus low). This classification was estimated using an established socioeconomic status consensus-based index (i.e., the SEIFA index of relative socio-economic advantage and disadvantage) [40]. Parks within each pair were randomized to one of the two conditions (i.e*.,* ‘Low’ or ‘Moderate’ implementation support). The randomization procedure was conducted by a researcher not part of the core research team. The randomization outcome for each location can be found in supplementary material 1. Data collection will be blinded to group allocation.

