#### ecofit app

2.5.1

The *ecofit* application has been updated based on feedback from the smartphone app used in the effectiveness trial [29,31] and the need to increase the scalability of its functions from a design perspective. The new *ecofit* platform can be accessed both via a smartphone app downloadable for apple and android devices, as well as via website browsers. The functionality has been improved and expanded upon compared with the previous app [31], and now includes a more scalable approach to tailoring workouts.

The new platform includes (i) videos with real people demonstrating the exercises in an outdoor gym or home-based setting, (ii) written instructions of each exercise alongside the videos, (iii) four different difficulty levels (i.e., level 1 to 4), (iv) ability to choose predetermined or ‘create your own’ workouts, (v) self-monitoring functions (i.e., goal setting and self-assessment tool), (vi) an exercise library, and (vii) resources based on behaviour change techniques [43]. Instead of a face-to-face introductory session, as was used in the effectiveness trial [31], the new *ecofit* platform includes a built-in function that guides users through the app upon registration. Alongside this, users will also have access to an introductory video explaining the purpose of *ecofit* and an onboarding video, which provides an overview of how to use the *ecofit* app. The app will be available to download free of charge, with no exclusion criteria. Informed consent will be collected via the app upon registration. See Fig. 3 for a screenshot of the *ecofit* app homepage and ‘progress’ section.

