#### Quick-response (QR) codes

2.6.2

QR codes will be placed next to or near the outdoor gyms included in the locations receiving Moderate implementation support. Scanning the QR code will automatically redirect park visitors to the *ecofit* website and provide information about how to download the app. In recent years, QR codes are becoming increasingly popular to use in various research fields and non-research settings [46]. Websites that include program information and resources have been used in other larger scale physical activity interventions [22].

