### Statistical analysis

2.9

Statistical analyses of the primary (i.e., reach) and secondary (except for fidelity) outcomes will be conducted with generalised linear models adjusted for the baseline value of the outcome using IBM SPSS Statistics version 30 (IBM Corporation, Armonk, NY) for Windows computers. These models will include fixed effect for study group, baseline value of the outcome, and stratification variables (i.e., high versus low SEIFA value). We will explore descriptive statistics and conduct a moderator analysis on the moderate implementation support strategies (i.e. face to face sessions, QR codes at park) to determine their independent impact on our primary outcome of park use. Additional exploratory sub-group analyses of the intervention effect on the primary (i.e., reach) and secondary outcomes (i.e., uptake, dose received, usage and impact) will be conducted using generalised linear models adjusted for the baseline value of the outcome (i.e., group-by-moderator) by gender (i.e., woman, man, unsure) and age (i.e., adults [18–59 years], and seniors [60 years or older]). Descriptive statistics will be used to examine the other secondary outcome of the study (i.e., fidelity) and the implementation determinants (i.e., acceptability, feasibility, dose satisfaction and cost). Sensitivity analyses will examine the robustness of the findings considering the quality of the outdoor gym facilities (based on the audit tool). Analysis of app usage data will include descriptive statistics and Cox Regression to examine time to non-usage attrition as in prior studies [51,52].

To detect a Cohen's d of 1 (strong effect), we estimate that ∼2 individuals will be observed using the outdoor gyms as intended per day per park (17 individuals in total in each group per day) assuming 80 % power and p = 0.05. Taking clustering by park into consideration and assuming an ICC of 0.05, then the design effect is 1.05, resulting in ∼3 individuals per day/park (24 individuals in total in each intervention group, total n = 48). From our previous work, this number is reasonable to expect [39,41].

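### Dose received (as a proportion or per-user mean) and impact are measured only in people who registered after randomisation, so the planned arm comparison of them is not a randomised one and its bias has no known direction

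*Protocol article*

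**What the plan says.** Order of events. Section 2.2 states "Randomization of the park location has already been conducted". Individuals enter later and by their own choice. Section 2.5.1 says "The app will be available to download free of charge, with no exclusion criteria" and "Informed consent will be collected via the app upon registration".

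Routes to registration. Both arms share a promotional campaign, of which section 2.2 says "this will serve as the primary recruitment strategy for the study". Only Moderate has two further routes:
- **QR codes.** Section 2.6.2: "QR codes will be placed next to or near the outdoor gyms included in the locations receiving Moderate implementation support". It adds "Scanning the QR code will automatically redirect park visitors to the" ecofit website, with information on downloading the app.
- **Sessions.** Section 2.6.1 describes three free group sessions, advertised by posters at the gyms and in surrounding suburbs. The session emails go to people who have already registered, so they do not alter who registers.

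Measures. In section 2.7.2.1 dose received is a number of logged workouts among participants; it "is also operationalized as the proportion of participants logging at least one workout in the app", read at three and six months. In section 2.7.3.2 impact is push-up and sit-to-stand performance that users enter in the app. Section 2.7.2.2 makes the number of registrations an outcome in its own right (uptake).

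Analysis. Section 2.9: "Statistical analyses of the primary (i.e., reach) and secondary (except for fidelity) outcomes will be conducted with generalised linear models", with terms for study group, baseline value and SEIFA stratum. Fidelity is the only secondary outcome that this sentence exempts, and the abstract names dose received and impact in the Low-versus-Moderate objective.

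**The concern.** Randomisation makes the parks and their surrounding populations comparable. It does not make the registrants comparable, because registering is a later event that the support model is meant to influence. Conditioning on registration means conditioning on something the arm may have changed. A group effect on a proportion of registrants, a mean per registrant or registrants' fitness then mixes two things: what the support model did to people who would have joined anyway, and who else it brought in.

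The planned covariates do not separate these. Workouts logged in the app have no value before registration, and the impact baseline is entered in the app after the person has joined. SEIFA describes the area, not the individual's decision to join.

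What is at stake is the message to councils, who are the intended users of the result. A group effect on dose received or impact would be read as an effect of the support model, and its sign could be wrong in either direction.

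**Working it through.** **The plan's own figure.** Section 2.9 gives a sample size for reach only. There is no expected value for dose received or impact to reproduce, so all inputs below are assumptions.

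**Set-up.** Let N be the registrants who would join under either arm, p0 their logging rate under Low, gain the rise in that rate under Moderate, E the extra registrants whom Moderate draws in, and pe their logging rate.

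- Low proportion = p0
- Moderate proportion = [N(p0 + gain) + E·pe] / (N + E)
- Moderate is below Low when N·gain + E·pe < E·p0, that is, when **E(p0 − pe) > N·gain**
- More people train in Moderate whenever N·gain + E·pe > 0

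Both conditions can hold together.

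**Illustrations with N = 200, p0 = 50%, E = 100** (z from independent users, unpooled SE, clustering ignored):

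| pe | gain | Low | Moderate | Difference | People training |
|---|---|---|---|---|---|
| 20% | 0 | 100/200 = 50% | 120/300 = 40% | −10 points | +20% |
| 30% | 0 | 100/200 = 50% | 130/300 = 43.3% | −6.7 points | +30% |
| 30% | 10 points | 100/200 = 50% | 150/300 = 50% | 0 | +50% |
| 70% | 0 | 100/200 = 50% | 170/300 = 56.7% | +6.7 points | +70% |

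- Row 1: SE = sqrt(0.25/200 + 0.24/300) = 0.0453, z = −2.21, p = 0.03.
- Row 2: SE = sqrt(0.25/200 + 0.2456/300) = 0.0455, z = −1.47, p = 0.14.
- Row 3: a real benefit among the original 200 shows as no difference, since 100 × (0.50 − 0.30) = 20 = 200 × 0.10.
- Row 4: the same selection produces an apparent gain, although nobody in the original 200 behaved differently.

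**Range.** Take N = 200, p0 from 40% to 60%, pe from 20% to 40%, and E of 50, 100 or 200. With no gain, Moderate lies 2 to 20 points below Low whenever pe < p0, and is equal when pe = p0. With a 5-point gain it runs from 17.5 points below to 4 points above. This grid never sets pe above p0, so it shows only one side of the bias; row 4 shows the other.

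**Per-user mean against total.** Suppose 200 users log 6 workouts each and Moderate adds 100 users who log 2 each. The Moderate mean is (1200 + 200)/300 = 4.67 against 6.0 in Low, while the total is 1400 against 1200. The mean reverses and the total does not.

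**Impact.** Suppose the mean fitness gain is 4.0 in Low. If Moderate lifts the original 200 to 4.5 and adds 100 users who gain 2, its mean is (900 + 200)/300 = 3.67, below Low although the original users did better.

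**The case against.** The strongest reply is that uptake is a planned secondary outcome at the same two time points. Multiplying uptake by the proportion recovers the number of people training: 200 × 50% = 100 against 300 × 40% = 120. Reach is an observed count at the park, and the cost-effectiveness analysis uses reach and uptake, not dose. Keeping uptake and engagement among adopters as separate constructs is also a legitimate choice. All of this stands, and it limits the harm. It does not change the planned analysis, which still estimates a group effect on the selected denominator. It also gives no way to recover a fair comparison of impact.

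A reader might infer more than the document supports:
- **That Moderate will look worse.** Nothing in the article says people who scan a QR code log less. They are already at an outdoor gym and might train more than letter-drop recruits. The sessions, where attendees can ask about the app, might also raise logging among people who would have joined anyway.
- **That the fall vanishes only if extra registrants log at the same rate as the rest.** It also vanishes if they log at a higher rate, or if the gain among the others is large enough.
- **That every count of workouts is affected.** A total has no registrant denominator. The article does not say whether a total or a per-user mean is meant, and a condensed article may leave that to the fuller plan.
- **That the arms recruit through separate channels.** The shared campaign is the primary route; Moderate adds to it.

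**Conclusion.** The point holds for the proportion of participants logging a workout, for any per-user mean of workouts and for impact. For these, the group effect in section 2.9 compares self-selected groups whose make-up the arm can alter. That conclusion rests on the protocol's own sequence and definitions, not on assumed numbers.

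The size and sign of the bias cannot be derived from the document. The illustrations run from 20 points against Moderate to 6.7 points in its favour, all on assumed inputs. The nominal p of 0.03 belongs to one chosen scenario; a neighbouring one gives 0.14, and both ignore clustering by park. They show that a reversal is possible, not that it is expected.

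Reach and a total count of logged workouts are not affected in this way. Because the problem is confined to secondary outcomes, it should be corrected but does not threaten the primary result.

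**What to change.** 1. **Dose received, arm comparison.** Analyse the number of different people logging at least one workout, and total logged workouts. Take each per park catchment, with a resident-population denominator that predates randomisation. The parks are already allocated, so draw catchments by one rule that ignores allocation.
2. **Registrant measures.** Report the proportion logging and the per-user means by arm as descriptive measures beside uptake, without a group-effect test.
3. **Impact.** State in section 2.9 that impact compares self-selected registrants and that a difference is not to be attributed causally to the support model. Adjusting for age and gender would not cure the selection.

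Cost: the workouts are already recorded in the app, and the denominator is a public population count, so no new data collection is needed. Two pieces of work come first. Catchments must be defined, and a rule must link each app user to an arm. The article gives no such rule, every gym is on the platform for both arms, and workouts can be done at home. One downside is that a catchment count combines uptake with engagement, which is why the within-arm proportion must still be shown.

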##### Uptake

2.7.2.2

‘Uptake’ will be defined as the total number of app registrations at three- and six-months post baseline. Only app registrations from the Newcastle and Lake Macquarie municipalities (i.e., based on postcode) and from the launch date of the promotional campaign will be included in the analysis. ‘Uptake’ will also be evaluated by the number of people attending the face-to-face workout sessions in the parks receiving Moderate implementation support by the three-month time-point. The fitness professionals conducting the park-based face-to-face workout sessions will collect count data on attendees, including perceived gender and age categories.

##### Fidelity of face-to-face delivery

2.7.2.3

A member of the research team will randomly observe each fitness professional on at least two occasions to assess how the individual conducted the workout sessions at the *ecofit* parks receiving Moderate implementation support. Adherence to the exercise protocol by the fitness professional will be measured as ‘yes’ or ‘no’ by the research team member.

#### Secondary intervention outcomes/measures

2.7.3

##### Usage

2.7.3.1

‘Usage’ will be evaluated by the number of views of the resource material (i.e., videos and text) across the *ecofit* platform at three- and six months.

##### Impact

2.7.3.2

‘Impact’ outcomes will be collected via the built-in self-assessment feature in the *ecofit* app at baseline, three and six-months. App notification will be sent at these time points to encourage users to conduct and enter their own self-assessed upper (i.e., push ups on toes or knees) and lower body (i.e., 60-sec sit-to-stand test) muscular fitness. The push-up and 60-sec sit-to-stand tests have demonstrated strong and moderate validity in a sample of community dwelling adults, respectively [50]. Impact is also considered to be a component of study effectiveness.

##### Acceptability, feasibility, and dose satisfaction of the app

2.7.3.3

Acceptability of the app will be evaluated using a process evaluation survey through the app (see supplementary material 4). Measures will include satisfaction with the content (i.e., exercises, workouts, resources) and app usability. Users will be prompted to complete the survey 6-weeks after registering an account, only data for users who have engaged with the app will be included.

#### Secondary implementation determinants

2.7.4

##### Acceptability, feasibility, and dose satisfaction of face-to-face sessions

2.7.4.1

All fitness professionals will be interviewed at the conclusion of all face-to-face training sessions; perceptions about acceptability, feasibility and satisfaction of delivering the training sessions will be explored. Acceptability and satisfaction will also be evaluated with a follow-up survey among participants who have engaged in at least one face-to-face workout session. Participants will complete these surveys directly following the face-face sessions by scanning a QR code and completing online. See supplementary material 5 for survey.

##### Cost-effectiveness

2.7.4.2

We will conduct a cost-effectiveness analysis by calculating the resources spent on design, adaption and implementation of the two implementation strategies. The outcomes of reach and uptake will be considered in the analyses.

### Data management plans

2.8

All data will be entered into a database using unique study codes and stored securely on a password protected computer. Only a limited group of researchers will have access to the database. If any important protocol modifications occur during this study, these will be updated on the Australian and New Zealand Clinical Trial Registry and the journal of publication. Before publication of the primary and secondary outcomes of this study, a deidentified dataset will be uploaded to an appropriate data repository.

### Statistical analysis

2.9

Statistical analyses of the primary (i.e., reach) and secondary (except for fidelity) outcomes will be conducted with generalised linear models adjusted for the baseline value of the outcome using IBM SPSS Statistics version 30 (IBM Corporation, Armonk, NY) for Windows computers. These models will include fixed effect for study group, baseline value of the outcome, and stratification variables (i.e., high versus low SEIFA value). We will explore descriptive statistics and conduct a moderator analysis on the moderate implementation support strategies (i.e. face to face sessions, QR codes at park) to determine their independent impact on our primary outcome of park use. Additional exploratory sub-group analyses of the intervention effect on the primary (i.e., reach) and secondary outcomes (i.e., uptake, dose received, usage and impact) will be conducted using generalised linear models adjusted for the baseline value of the outcome (i.e., group-by-moderator) by gender (i.e., woman, man, unsure) and age (i.e., adults [18–59 years], and seniors [60 years or older]). Descriptive statistics will be used to examine the other secondary outcome of the study (i.e., fidelity) and the implementation determinants (i.e., acceptability, feasibility, dose satisfaction and cost). Sensitivity analyses will examine the robustness of the findings considering the quality of the outdoor gym facilities (based on the audit tool). Analysis of app usage data will include descriptive statistics and Cox Regression to examine time to non-usage attrition as in prior studies [51,52].

To detect a Cohen's d of 1 (strong effect), we estimate that ∼2 individuals will be observed using the outdoor gyms as intended per day per park (17 individuals in total in each group per day) assuming 80 % power and p = 0.05. Taking clustering by park into consideration and assuming an ICC of 0.05, then the design effect is 1.05, resulting in ∼3 individuals per day/park (24 individuals in total in each intervention group, total n = 48). From our previous work, this number is reasonable to expect [39,41].

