### Experimental design

2.1

We will evaluate the implementation of *ecofit* using a hybrid type III implementation-effectiveness trial [37] involving 16 outdoor gym locations randomized to either the (i) ‘Low’ or (ii) ‘Moderate’ implementation support model. Assessments will be conducted at baseline, 3-months (primary and secondary outcomes) and 6-months (secondary outcomes only) and will commence in mid-2024. This implementation-effectiveness trial will be conducted across all outdoor gym locations (N = 16) in the Newcastle City (population n = 173,251) and Lake Macquarie (population n = 202,680) local government municipalities, New South Wales (NSW), Australia. The Standards for Reporting Implementation Studies (StaRI) initiative will be used in the reporting of this study [38]. Our study has received ethical approval from the University of Newcastle Ethics committee (H-2018-0060). The trial has been registered with the Australian and New Zealand Clinical Trial Registry (ANZCTR) (ACTRN12624000261516).

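### Parks are randomised, but the stated models make no allowance for park, so group tests on individual app users would be too precise

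*Protocol article*

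**What the plan says.** The unit of allocation is the park. Under Experimental design the trial is described as "involving 16 outdoor gym locations randomized to either the (i) ‘Low’ or (ii) ‘Moderate’ implementation support model", and under Recruitment, randomization and blinding: "Parks within each pair were randomized to one of the two conditions". That gives 8 pairs and 8 parks per arm.

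The Statistical analysis section recognises that observations within a park may be alike. Its sample size is worked out "Taking clustering by park into consideration and assuming an ICC of 0.05".

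The same section sets one model class, the generalised linear model, for reach and for every secondary outcome except fidelity. On the terms it says: "These models will include fixed effect for study group, baseline value of the outcome, and stratification variables (i.e., high versus low SEIFA value"). The exploratory gender and age analyses of reach, uptake, dose received, usage and impact use the same class with a group-by-moderator term. Nowhere does the article name a random effect for park, generalised estimating equations, a cluster-robust variance or analysis of park summaries.

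The outcomes sit at different levels. Reach is summed to one total per park per time point (Reach). Impact is recorded person by person: these "outcomes will be collected via the built-in self-assessment feature in the" app. Dose received includes workouts logged by participants and the proportion logging at least one.

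**The concern.** When parks are randomised, a difference between arms has to be judged against the variation between parks. A generalised linear model on individual app users, with only group, baseline and SEIFA, judges it against the variation between users. If users of the same park resemble each other at all, the standard error of the group effect is too small. Chance park-to-park differences in muscular fitness or logged workouts could then be reported to councils as an effect of the extra support.

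A related issue arises if reach by gender or age is analysed by splitting each park's total into several counts in one model. Those counts share a park, while gender and age vary within it. Ignoring the park then makes the group effect too precise and the group-by-subgroup interaction too imprecise.

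**Working it through.** **Step 1: the plan's own figure.** Inputs from Statistical analysis: "To detect a Cohen's d of 1 (strong effect"), "assuming 80 % power and p = 0.05", and "17 individuals in total in each group per day" before clustering.
- A two-sided two-sample t-test with d = 1 has power 0.781 at 16 per group and 0.807 at 17, so 17 is reproduced.
- Design effect DE = 1 + (m − 1) × ICC. With m = 2 per park, DE = 1 + 1 × 0.05 = 1.05, as stated.
- 17 × 1.05 = 17.85 per group; 17.85 / 8 parks = 2.23 per park. Rounded up to 3, this is 24 per group and 48 in total, as stated.

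Clustering by park is therefore part of the planning. The ICC is a planning value for people observed at the gyms, not for app outcomes.

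**Step 2: cost of leaving park out of a user-level comparison.** Actual type I error of a nominal 5% two-sided test = 2 × [1 − Φ(1.96 / √DE)]. The number of users per park, m, is an assumption because the protocol gives none. The ICC of 0.05 is also an assumption for these outcomes.

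| ICC | m | DE | √DE | Type I error |
|---|---|---|---|---|
| 0.05 | 3 | 1.10 | 1.049 | 6.2% |
| 0.05 | 10 | 1.45 | 1.204 | 10.4% |
| 0.05 | 20 | 1.95 | 1.396 | 16.0% |
| 0.05 | 30 | 2.45 | 1.565 | 21.0% |
| 0.01 | 30 | 1.29 | 1.136 | 8.4% |

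**Step 3: check by simulation.** With 8 against 8 parks, normal outcomes, equal park sizes and 10,000 replicates, the analysis ignoring park rejected in 5.9% (m = 3), 10.4% (m = 10) and 21.7% (m = 30) of trials at ICC 0.05, and in 8.1% at ICC 0.01 with m = 30. A t-test on the 16 park means (14 degrees of freedom) rejected in 4.7% to 5.5% across all settings.

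**Step 4: split counts.** Suppose each park contributes two rows to one model, with correlation ρ between them. The true standard error of the group effect is √(1 + ρ) times the naive one, and that of the interaction is √(1 − ρ) times the naive one. Simulated rejection at nominal 5% (20,000 replicates):

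| ρ | Group effect | Interaction |
|---|---|---|
| 0.05 | 5.6% | 4.3% |
| 0.2 | 7.4% | 2.8% |
| 0.5 | 10.6% | 0.7% |

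The protocol gives no value for ρ.

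**The case against.** A fair defence has four parts.

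1. *The ICC belongs to reach.* The 0.05 was assumed for observed gym users, and none is assumed for push-ups, sit-to-stand or logged workouts. A reader might infer that the secondary models contradict the protocol's own ICC. The documents do not support that, and 0.05 serves here only to illustrate. What remains is that parks are randomised and the stated models have no park term.

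2. *The list of terms may not be exhaustive, and an analysis plan could add to it.* This has some force for a condensed article. But the article fixes the model class and the terms for the secondary outcomes, and an analysis that follows them as written treats users as independent.

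3. *Nothing places an app user in a park.* Postcode restricts registrations to the two municipalities and targets session emails, all gyms appear on the app whatever their allocation, and workouts may be done at home or anywhere. This stands, and it shapes the fix. It does not rescue the model, because comparing arms on app users already requires a rule linking users to parks or arms.

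4. *Some outcomes may be aggregates.* Registrations, resource views and a proportion of participants could each be analysed as one figure per park, and then no inflation arises. This stands; the point is confined to outcomes analysed on individuals.

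**Conclusion.** The point holds for secondary outcomes analysed on individual app users, chiefly impact and logged workouts. Analysed as written, their group effects would be too precise. The size depends on two quantities that the protocol does not give for these outcomes: users per park and the ICC. Over the range shown, type I error runs from about 6% (3 users per park, ICC 0.05) to about 21% (30 users, ICC 0.05), and is about 8% at ICC 0.01 with 30 users. These figures assume that users are nested in parks and that parks are of equal size. Impact relies on voluntary self-assessment, so the number of completers per park could be small and the inflation modest. A claim that significance would be declared far too often goes beyond the documents.

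For reach by gender or age the point is conditional. It applies only if several counts per park enter one model; it is small at low within-park correlation, and those analyses are exploratory.

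A reader might also infer that the primary analysis is invalid for this reason. It is not: overall reach has one total per park, so there is no within-park replication to account for.

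**What to change.** First, state a prespecified rule that assigns each app user to a park, for example by registration postcode. Say how it treats users who could belong to more than one park and those who train only at home.

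Then state that every outcome analysed below park level, and reach split by gender or age, will be analysed in one of two ways:
- a generalised linear mixed model with a random intercept for park, with the group effect tested on small-sample, between-park degrees of freedom (at most 16 − 2 = 14, fewer once park-level covariates enter); or
- aggregation to one value per park (for split reach, one value per park for each contrast tested).

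Overall reach, and any other outcome analysed as one value per park, needs no park term; say so explicitly.

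The cost is a change of wording. The named software fits these models, and neither design nor fieldwork changes, provided the assignment rule uses information already collected at registration. The downside is wider confidence intervals for group effects on user-level outcomes, which reflects the information that 16 parks can give.
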